#### **5.6. discontinuation of protocol treatment**

The investigator or subinvestigator will discontinue the study drug if the investigator or subinvestigator determines that continuation of protocol treatment is not feasible for any of the following reasons. The date, reason, and progress of discontinuation will be documented in the medical record and the case report form (CRF), and necessary tests will be performed at the time of discontinuation or dropout to evaluate efficacy and safety.

If the drug is discontinued due to the occurrence of an adverse event, the patient should be followed up as much as possible until the current status is restored.

(1) When a research subject or a surrogate withdraws from participation in clinical research or withdraws his/her consent.

(2) When it is found that eligibility is not satisfied after registration

(iii) When the underlying disease is completely cured and there is no longer a need for continued administration

(iv) When it is determined that continued administration of the test drug is not desirable due to worsening of the underlying disease

(5) When it is difficult to continue the clinical research due to exacerbation of complications

(6) When it is difficult to continue the clinical research due to adverse events

(vii) In case of significant non-adherence (when it is determined that less than 70% of the total scheduled doses will be taken or more than 120% of the total scheduled doses will be taken)

(viii) If the research subject does not come to the hospital due to relocation, etc.

(ix) When the entire clinical research is discontinued

(10) When the principal investigator determines that it is appropriate to discontinue the clinical research for other reasons

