## **10.2. population to be analyzed**

The primary analysis of the primary and secondary endpoints will be performed on the Full Analysis Set (FAS). Analysis will also be performed on the Per Protocol Set (PPS) and compared with the FAS to confirm the stability and sensitivity of the analysis results.

The FAS is defined as a population that excludes from all enrolled cases any case that falls into one of the following categories: (1) cases with a confirmed diagnosis of a disease that is not eligible, (2) cases that violate important exclusion criteria, (3) cases that have never received protocol treatment since enrollment, or (4) cases with no data at all since enrollment.

The PPS will be defined as patients who meet the minimum requirements for key variables in the study protocol, for whom protocol treatment was not possible or was discontinued, but who have completed MRI evaluation and have no serious protocol violations regarding eligibility criteria, concomitant prohibited drugs, etc. The Safety Analysis Set (SAS) is defined as all enrolled patients, excluding those who have never received protocol treatment since enrollment.

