### **10.3.2. secondary analysis methods for the primary endpoint**

For reference, the same analysis as in 10.3.1 will be performed with the PPS as the population to be analyzed.

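### As worded in protocol 10.2, the Per Protocol Set consists of children whose treatment was not possible or was stopped, so the reference PPS analysis cannot properly check the FAS result

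*Protocol*

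**What the plan says.** Section 10.2 makes the FAS the primary population and adds a PPS, whose results are to be "compared with the FAS to confirm the stability and sensitivity of the analysis results". The definition begins "The PPS will be defined as patients who meet the minimum requirements for key variables in the study protocol" and continues "for whom protocol treatment was not possible or was discontinued, but who have completed MRI evaluation and have no serious protocol violations"; the violations it names concern eligibility and prohibited concomitant drugs. It does not say what the minimum requirements are, and it states no completion or adherence condition.

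The FAS, defined in the same section, removes among others "cases that have never received protocol treatment since enrollment".

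Section 10.3.2 states, for reference only, that "the same analysis as in 10.3.1 will be performed with the PPS as the population to be analyzed".

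Elsewhere, 5.6(vii) treats as significant non-adherence a finding that "less than 70% of the total scheduled doses will be taken or more than 120% of the total scheduled doses will be taken". Section 9.2 sets taking at least 70% of medication as the adherence endpoint, and 10.3.4 lists adherence as a subgroup factor for response. No other section defines the PPS differently.

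**The concern.** A per-protocol set normally holds the patients who were treated as planned, so that its result can be set beside the FAS result to see how far departures from the plan matter. Here the treatment clause points the other way: it names the children who could not take the drug or stopped it, and the only thing asked of them is a completed MRI and no serious violation.

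The trial is open-label and single-arm with about 18 children in the analysis, and the PPS is the only alternative analysis of the primary endpoint that the protocol states. If the sentence stays as it is, someone has to decide what it means, possibly after the responses are known. The readings can give very different answers from the same data.

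**Working it through.** **1. The plan's own figure.** Section 10.1 plans for 9 responders among 18 analysed. Section 10.3.1 specifies an exact binomial method with a two-sided 90% interval. The Clopper-Pearson limits for x responders among n are

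- lower = the 0.05 quantile of Beta(x, n − x + 1)
- upper = the 0.95 quantile of Beta(x + 1, n − x)

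For 9/18 this gives 29.12% to 70.88%. It agrees with the stated 29.1% and 70.8%, the latter truncated rather than rounded. The width is 70.9 − 29.1 = 41.8 points.

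**2. Literal reading: only children not treated or discontinued, with an MRI.** The protocol gives no discontinuation rate, so 5% to 30% is assumed. It is also assumed that every discontinued child has an MRI and that about half respond, rounded down. PPS size = 18 × rate, rounded. The last two columns show the complement, that is, the children who were treated through.

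| Assumed rate | Literal PPS | Example, exact 90% CI | Width (points) | Treated through | Example, exact 90% CI |
|---|---|---|---|---|---|
| 5% | 0.9 → 1 | 0/1: 0% to 95% | 95 | 17 | 8/17: 26.0% to 68.9% |
| 10% | 1.8 → 2 | 1/2: 2.5% to 97.5% | 95 | 16 | 8/16: 27.9% to 72.1% |
| 15% | 2.7 → 3 | 1/3: 1.7% to 86.5% | 85 | 15 | 7/15: 24.4% to 70.0% |
| 20% | 3.6 → 4 | 2/4: 9.8% to 90.2% | 80 | 14 | 7/14: 26.4% to 73.6% |
| 30% | 5.4 → 5 | 2/5: 7.6% to 81.1% | 73.5 | 13 | 6/13: 22.4% to 71.3% |

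The chance that the literal set is empty is (1 − rate)^18: 0.95^18 = 40%, 0.90^18 = 15%, 0.80^18 = 2% and 0.70^18 = 0.2%.

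**3. Reading the clause as *even if treatment was not possible or was stopped*.** Completers are now in. The PPS then requires a completed MRI and no serious violation. The FAS has already removed ineligible diagnoses and breaches of important exclusion criteria. Section 10.3.6 does not fill in missing values, so unless a missing scan is counted as non-response the FAS rate also rests on children with an MRI. What remains different is mainly the removal of children given prohibited treatment. Children who took little drug stay in. They can well have a scan: 5.6 calls for tests at discontinuation, the schedule in 6.2 lists MRI at that time, and 5.3.5 continues monitoring after the drug is stopped for poor adherence.

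**4. How far the readings can diverge (hypothetical data).** Take 18 FAS children, all with an MRI and no violations. Four discontinue and none of them responds; 9 of the 14 completers respond.

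- FAS: 9/18 = 50%
- PPS, literal: 0/4 = 0%
- PPS, *even if* reading: 9/18 = 50%
- PPS of completers: 9/14 = 64%

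**5. Subset check.** If the words on treatment not being possible cover a child who never started, that child can be in the PPS but is removed from the FAS by its third exclusion. The PPS is then not contained in the FAS.

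**The case against.** The English is visibly a rough translation, and the clause has a concessive shape. The sponsor may well have meant to keep discontinued children provided they were scanned, perhaps deliberately. On that reading the comparison is not empty: it would still show the effect of removing children given prohibited treatment and, if missing scans count against response in the FAS, of removing children without an MRI. Low adherence is also not ignored, because 10.3.4 plans response rates by adherence. The undefined minimum requirements in 10.2 could be meant to include adherence. All of this stands, and it limits the point.

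Four stronger readings are tempting, and the protocol does not support them.

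- *The primary result is compromised.* It is not. The primary analysis uses the FAS, the sample size rests on the precision of 9/18, and the PPS analysis is for reference.
- *The literal PPS would have 0 to 2 children, because 20 are enrolled and 18 analysed.* That allowance in 10.1 is for cases excluded from analysis, not for children who stop treatment and have an MRI.
- *Agreement or disagreement between PPS and FAS would mean nothing.* That goes too far for the *even if* reading, for the reasons just given.
- *The PPS certainly contains never-treated children.* The wording permits it, but it takes a child with no dose and a completed MRI evaluation, which should be rare.

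What the objection does not rescue is the text itself. Whatever was intended, the protocol states the set in words that, if followed, leave out the children who completed treatment.

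**Conclusion.** The PPS definition in 10.2 is wrong as written and should be corrected before analysis. Taken literally, it yields about 1 to 5 of 18 children and intervals roughly 73 to 95 points wide, against 41.8 for the planned FAS interval. These sizes rest on the assumed 5% to 30% discontinuation rate, a scan in every discontinued child and about half responding. Read generously, it comes close to repeating the FAS analysis and does not separate children treated as planned from those who were not. In neither form can it properly serve as the stability check described in 10.2. The consequence is confined to that reference analysis.

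**What to change.** Rewrite the PPS sentence in 10.2 before any analysis so that the set is

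- a subset of the FAS,
- made up of children treated according to protocol,
- with evaluable baseline and 6-month (Day 168) MRI,
- with no prohibited concomitant treatment and no serious eligibility violation.

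Delete the clause on treatment not being possible or being discontinued, or reword it to match.

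State an adherence criterion for the analysis set. One example, in line with 9.2, is at least 70% of the doses scheduled up to the end, or the protocol-specified stop, of treatment. The denominator matters. Requiring 70% to 120% of the full six-month schedule and dropping every discontinued child would remove children stopped for cure or for worsening under 5.6(iii) and (iv), so that membership would depend on outcome. For the same reason, say how a child is handled whose only follow-up scan was taken at discontinuation. The criterion defines an analysis set only and changes no treatment rule.

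The cost is one rewritten sentence with its adherence criterion. No data collection, sample size or primary analysis changes.

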## **10.3 Analysis Items and Methods**

### **10.3.1. primary endpoint primary analysis method**

For the primary endpoint of the study, the response rate will be based on whether or not patients achieve a reduction in lymphatic malformation volume by volumetry of at least 20% from the pre-treatment level at 6 months of treatment with the drug. An exact method based on a binomial distribution will be used for interval estimation. The significance level for the main analysis is 5% one-sided, and the corresponding two-sided 90% confidence interval is calculated.

### **10.3.2. secondary analysis methods for the primary endpoint**

For reference, the same analysis as in 10.3.1 will be performed with the PPS as the population to be analyzed.

### **10.3.3 Analysis Methods for Secondary Endpoints**

#### **1. reduction of more than 50% of the volume**

For each case, the presence or absence of a reduction of 50% or more in the volume of lymphatic malformations by volumetry at 6 months of drug administration from before the start of treatment is determined, and based on this, the percentage of volume reduction of 50% or more is determined. For interval estimation, an exact method based on binomial distribution is used and two-sided 95% confidence intervals are calculated.

#### **2. shrinkage rate**

---

For each case, determine the percentage reduction in volume of lymphatic malformations by volumetry at 6 months of drug administration from before the start of drug administration.

3. 10% improvement in QOL

Use EQ-5D-5L Japanese version for Japan.

Depending on the respondents' understanding of the questionnaire, Effective\_Japan (Japanese) EQ-5D-5L Paper Self-Complete v1.2 or Effective\_Japan (Japanese) EQ-5D-5L Paper Proxy2 v1.1 is used to determine the percentage of improvement in quality of life by 10% or more.

4. safety

For adverse events, determine the type and frequency along with a list. If necessary, use an accurate method based on a binomial distribution when determining confidence intervals .

5. medication adherence

Obtain numerical values for medication adherence. If necessary, use an exact method based on a binomial distribution when determining confidence intervals.

### 10.3.4 Subgroup Analysis

Obtain response rates as in 10.3.1 for each of the following subgroups.

- gender
- Site of lesion
- Medication adherence
- Age
- Nature of lesion (cystic lesions are defined as cysts >2 cm in diameter)

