## 9.2. secondary endpoints

1. percentage decrease of more than 50% of volume

2. lesion reduction rate

3. 10% improvement in quality of life associated with treatment

4. safety of administration of koshuizhuyuu

5. adherence to the administration of Koshuizhuyuu (percentage of patients who were able to take

---

at least 70% of their medications)

Rationale: 3) Even if there is no marked change in size, QOL and symptom improvement has been reported, so it was set as a secondary endpoint; 4) Pseudohyperaldosteronism is known to be a major side effect of Eppikajutsuto, but its occurrence in children is not well reported.

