## **10. statistical considerations**

### **10.1 Basis for Setting Target Number of Cases**

In our retrospective case series study, the response rate (20% volume reduction at 6 months) to treatment with Eppikajutsuto in LM patients was 83% (in submission). Conservatively taking into account the overestimation tendency of the retrospective study design of prior reports, we expect a response rate of at least 50% with this treatment in the study's patient population. In the same study, none of the patients had a response to no treatment, and both patients had an increasing trend. Considering the exploratory nature of this study, the first prospective clinical trial, the number of patients will be designed based on accuracy. The lower limit of the two-sided 90% confidence interval (corresponding to a one-sided significance level of 5%) is 29.1% (the upper limit is 70.8%) if 9 patients respond (response rate of 50%) in the 18 patients in the analysis.

Considering that the main purpose of this exploratory study is to collect information that can be used for the next phase of the study, we believe that 18 cases is an appropriate number of cases. Since the number of patients seen annually at each site is approximately 5 cases each, it is possible to enroll the target number of cases in 3 years.

Based on the above considerations, the target number of cases was set at 20 to ensure accuracy in case a few cases were excluded from the analysis.

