#### **10.1.1 Reestablishment of target number of cases**

As mentioned in 10.1, considering the rarity of the subject cases in this study, we believe that the number of cases of 20 is close to the upper limit from the viewpoint of feasibility. On the other hand, considering that the main purpose of this study is to collect information that can be used for the next phase, although it is positioned as an exploratory study, the collection of exploratory data that contributes to the identification of subpopulations with higher potential for efficacy is one of its important objectives, and a larger number of cases would be preferable as long as feasibility permits.

Based on the above considerations, if it becomes clear during the study period that the target number of 20 cases can be enrolled earlier than previously expected, the target number of cases will be considered for re-setting according to the progress at that point in time. From the viewpoint of feasibility, we currently plan to slightly increase the target number of patients at that time as well. However, we will consider re-setting the target number of patients appropriately according to the information that is updated and accumulated both inside and outside the study up to that point.

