### 10.3.5. significance level

Unless otherwise noted, the significance level is 5% one-sided, and the confidence coefficient for the confidence interval is correspondingly 90% two-sided.

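### Section 10.3.4 describes subgroups only by their 20% response rate, so the percentage volume reduction measured in each child goes unused for the subpopulation objective, and no between-subgroup difference is estimated

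*Protocol*

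**What the plan says.** Section 10.1.1 of the protocol, arguing for a possible increase beyond 20 cases, states that "the collection of exploratory data that contributes to the identification of subpopulations with higher potential for efficacy is one of its important objectives".

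Section 10.3.4 is the only place in the protocol that describes a subgroup analysis. It reads "Obtain response rates as in 10.3.1 for each of the following subgroups" and lists sex, site of lesion, medication adherence, age and nature of lesion. Section 10.3.1 defines the measure carried over as a "reduction in lymphatic malformation volume by volumetry of at least 20% from the pre-treatment level at 6 months", and adds: "An exact method based on a binomial distribution will be used for interval estimation". Under section 10.3.5, "the significance level is 5% one-sided, and the confidence coefficient for the confidence interval is correspondingly 90% two-sided".

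The continuous outcome exists. Section 9.2 lists the "lesion reduction rate" as a secondary endpoint, and item 2 of section 10.3.3 has the percentage volume reduction at 6 months determined for each case. Neither section connects it to the subgroups. No contrast or test between subgroups is named anywhere.

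**The concern.** Looking for subpopulations with higher potential for efficacy is a comparative question. The protocol answers it with separate proportions, each from a fraction of about 18 children, and estimates no difference between them. A child whose lesion shrinks by 21% and one whose lesion shrinks by 90% count the same; a child at 19% counts the same as one whose lesion grows. Age, a continuous variable, has to be grouped before it can yield rates at all.

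Section 10.1.1 regards 20 cases as close to the feasible maximum, so extra information has to come mainly from using the measurements better. At stake is how much the trial can tell the next phase about which lesions and which children respond. The primary result is not affected.

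**Working it through.** **1. The plan's own figure.** The Clopper-Pearson 90% interval for x of n runs from the 5% quantile of Beta(x, n−x+1) to the 95% quantile of Beta(x+1, n−x). For 9 of 18 this gives 29.12% to 70.88%. Section 10.1 states that the lower limit "is 29.1% (the upper limit is 70.8%) if 9 patients respond (response rate of 50%) in the 18 patients in the analysis". The figure reproduces; the upper limit is truncated rather than rounded.

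**2. What the planned display can show.** The same formula for subgroups of 9 gives:
- 6/9: 34% to 90%; 3/9: 10% to 66%
- 7/9: 45% to 96%; 2/9: 4% to 55%

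Both pairs overlap. Summing the binomial probabilities of all outcomes in which the two intervals separate in the right direction gives 16% at true rates of 70% v 30%, 31% at 75% v 25% and 50% at 80% v 20%. Non-overlap is a stricter criterion than a test of the difference, so these figures describe the display and are not the power of a comparison.

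**3. Binary against continuous.** The protocol gives no subgroup sizes, subgroup effects or SD of volume change. The following are assumptions: 18 analysed children (section 10.1), splits of 9 v 9 or 12 v 6, a normal volume change with equal SD cut at the response threshold, and one-sided 5%.

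- Standardised difference: d = z(p1) − z(p2). For 70% v 30%, d = 0.524 + 0.524 = 1.05.
- t-test: noncentrality = d × √(n1·n2/(n1+n2)) = 1.049 × √4.5 = 2.225, with 16 degrees of freedom and critical value 1.746. Power is 69%.
- Fisher exact and uncorrected chi-square: full enumeration of the 2×2 tables.

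| Split | True rates | Fisher | Chi-square | t-test | Fisher/t | Chi-square/t |
|---|---|---|---|---|---|---|
| 9 v 9 | 65% v 35% | 0.194 | 0.357 | 0.468 | 0.41 | 0.76 |
| 9 v 9 | 70% v 30% | 0.339 | 0.536 | 0.686 | 0.49 | 0.78 |
| 9 v 9 | 75% v 25% | 0.525 | 0.719 | 0.863 | 0.61 | 0.83 |
| 12 v 6 | 70% v 30% | 0.292 | 0.560 | 0.642 | 0.45 | 0.87 |

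Running 12 v 6 at the other two contrasts by the same method moves the outer limits only slightly, to 0.39 for Fisher (65% v 35%, 0.169/0.433) and 0.90 for chi-square (0.390/0.433).

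**4. Sensitivity.**
- Larger contrast: at 80% v 20% (9 v 9) the ratios rise to 0.75 and 0.90.
- Higher overall response: for a normal outcome the asymptotic relative efficiency of the cut outcome is φ(z)²/(p(1−p)). At p = 50% it is 0.399²/0.25 = 0.64. At 83%, the retrospective response rate quoted in section 10.1, it is 0.253²/0.141 = 0.45. At 95% v 60% (9 v 9) the powers are 36%, 57% and 88%.
- Bimodal response (simulated mixtures of responders and non-responders, 9 v 9): chi-square/t is 0.99 to 1.09 and Fisher/t is 0.69 to 0.81. Under this model the chi-square comparison loses essentially nothing.
- Ranks instead of t: for a normal percentage change with SD 20 points, a difference of 20 points and a centre at the threshold, the rank test has 0.597 against 0.649 for t, 0.505 for chi-square and 0.314 for Fisher. Most of the gain over Fisher remains.

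**The case against.** Section 10.3.4 plans descriptive rates with exact intervals. It plans no comparison, so no power is being spent, and Fisher, chi-square and the t-test are all brought in from outside. This stands, and it is why the loss is stated as information, with power ratios only as a gauge.

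A reader might infer that the trial pursues its subpopulation objective with a fixed share of the attainable power, say half to three quarters. The documents do not support that. The ratio depends on the test, the split, the contrast and the distribution, and can reach 1 or slightly more.

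A reader might also infer that the plan will fail its own objective. Section 10.1.1 promises only data that contribute to identifying subpopulations, section 1 lists no subgroup aim, and percentage reduction is collected for every case. Part of the imprecision comes from 18 children and not from the choice of outcome: even the continuous comparison has only 47% power at 65% v 35%.

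Reporting exploratory subgroups on the primary endpoint is conventional, and the statistical analysis plan may add detail such as age categories. That tempers the weight of the point without removing it. The protocol itself chooses the subgroup outcome and method, and the choice leaves out a more informative measure that it already collects. No figure for the loss from grouping age can be given, because the protocol does not say how age will be cut.

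**Conclusion.** The point holds as one of lost information. As written, section 10.3.4 restricts subgroup results to 20% response rates with exact intervals, leaves the per-child percentage volume reduction unused for the objective in section 10.1.1, and estimates no difference between subgroups. Under a normal model with 18 children, the relative power in the four scenarios is about 0.4 to 0.6 against Fisher and 0.76 to 0.87 against chi-square. The loss is larger if response is nearer 83%, and close to nil against chi-square if response is bimodal. Nothing here contradicts another part of the protocol or bears on the primary analysis. It is a worthwhile improvement to an exploratory analysis and does not indicate that the trial is unsound.

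**What to change.** Keep the response-rate table in section 10.3.4 and add the following, labelled exploratory:

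- For sex, site of lesion, nature of lesion and medication adherence: the 6-month percentage volume change by subgroup, with between-group differences and 90% intervals. Use percentage change itself or a rank-based method. A log volume ratio is undefined at zero volume, and section 5.6 (iii) foresees complete cure; percentage change and ranks both keep such a lesion in the analysis. Site may have more than two levels, so name the contrasts to be reported.
- For age: the association with volume change as a continuous variable, with a 90% interval.

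The cost is a few lines of protocol or analysis-plan wording and minor programming, with no new scans, visits or patients. The downside is a few more exploratory estimates without multiplicity control, which the label should make plain.

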## 1. purpose

To evaluate the efficacy, dose-response, and safety of Eppikajutsuto in patients with lymphangitic malformations (LM) in an open-label, pre- and post-administration study. The primary endpoint will be response from baseline in tumor volume by volumetry. Secondary endpoints will be 1. 50% or greater volume reduction, 2. shrinkage rate, 3. 10% improvement in quality of life, 4. safety, and 5. adherence to medications.

---

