#### 2.4. Issues, uncertainties, etc. in the current standard of care that lead to the need for such clinical research

While the standard therapies that have been implemented to date, as described above, are burdensome to patients in terms of side effects and cost, Eppikajutsuto has a high potential to solve these problems.

We were the first in Japan to report the effect of Echisukayaku-zhuyu on lesion reduction in mediastinal LM patients (Figure 1). Subsequently, many institutions have used Echisuyu-Kazhu-to, and in several retrospective case studies, we reported that reduction in mass size was observed in all 2, 8, and 9 cases, respectively. Based on these findings, it was inferred that an increased dose was necessary to achieve a reduction in size. Therefore, in this study, the dose was set at 0.6 g/kg/d in an exploratory manner. Although the insurance coverage for the use of extract is 7.5 g/d, we do not consider this to be particularly problematic, since the dosage is allowed to be increased as needed. The reason for this is that the subject of this study is limited to children, and the dose is doubled at 25 kg when the dose per body weight is doubled, but in this study, the dose is 7.5 g/day at 12.5 kg, so the dose was reduced at 12.5 kg or more. Therefore, the treatment above 12.5 kg can be regarded as treatment at a reduced dose, and it may be possible to evaluate this depending on the number of cases accumulated. There have been no reports of adverse drug reactions at doses such as 0.75 g/kg/d or 7.5 g/d for this dose.

We also reported an infant whose cervical LM was markedly reduced by an increased dose of Koshuizhuyu-tou. Furthermore, we also suggest an mTOR inhibitory effect by Koshui-Kazhu-tan in oral cancer cells.

[figure not shown]

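### Section 10.3.4 lists medication adherence, which arises during treatment and can depend on lesion course, as a subgroup factor, while the stated dose-response aim has no analysis by weight or dose per kg

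*Protocol*

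**What the plan says.** Section 10.3.4 of the protocol instructs: "Obtain response rates as in 10.3.1 for each of the following subgroups". The list is gender, site of lesion, "Medication adherence", age and nature of lesion. Section 10.3.1 supplies the method: the proportion with at least a 20% volume reduction at 6 months, with an exact two-sided 90% interval. Section 10.3.4 gives no cut-off or denominator for adherence.

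Section 5.6 lists the grounds on which the investigator may stop the drug. Two concern the course of the lesion. Ground (iii) is full resolution, after which the drug has no further purpose. Ground (iv) is deterioration, in these terms: "When it is determined that continued administration of the test drug is not desirable due to worsening of the underlying disease".

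Ground (vii) concerns intake and applies "when it is determined that less than 70% of the total scheduled doses will be taken", or more than 120%. The adherence endpoint in 9.2 also uses 70%.

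Section 10.1.1 says of the exploratory data that "the identification of subpopulations with higher potential for efficacy is one of its important objectives".

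Section 1 opens with "To evaluate the efficacy, dose-response, and safety of Eppikajutsuto". Section 2.4 notes that the daily cap is reached at 12.5 kg, so that "the treatment above 12.5 kg can be regarded as treatment at a reduced dose", and adds that this might be evaluated if case numbers allow. Neither weight nor dose per kg appears anywhere in 10.3.

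**The concern.** Four of the five listed factors can be known before the first dose. Adherence cannot. If a child stops because the lesion has worsened or resolved, and intake is then divided by all the doses that had been scheduled, low adherence is partly a record of the outcome. Response rates by adherence would then partly display the stopping grounds of 5.6, not the effect of taking the drug. Such a stratum also cannot be used to choose patients at entry, which is the use section 10.1.1 has in mind.

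Meanwhile, a factor that is known at entry and bears on a stated aim is not listed. All children follow one dosing rule, so the planned variation in dose per kg comes from the cap, through body weight. Without a split by weight or dose per kg, the dose-response part of the purpose has no analysis in section 10.3.

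**Working it through.** **Inputs from the protocol.** 20 patients planned and 18 in the precision calculation (10.1); expected response 50% (10.1); exact 90% interval (10.3.1); 0.6 g/kg/day (2.4); cap 7.5 g/day (5.3.3); weight limit 25 kg (3.1); 70% adherence threshold (5.6, 9.2); last treatment visit Day 168 (6.1).

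**1. The plan's own interval.** For 9/18, the Clopper-Pearson limits are the 5% quantile of Beta(9, 10) and the 95% quantile of Beta(10, 9), which are 29.12% and 70.88%. Section 10.1 states 29.1% and 70.8%. These agree, apart from truncation of the upper limit.

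**2. When perfect intake would count as low.** This takes total scheduled doses as denominator and 70% as cut-off, which 10.3.4 does not fix. With six months as 183 days, 0.70 × 183 = 128 days. With 168 days, 0.70 × 168 = 118 days. A child who takes every dose but stops before then falls in the low stratum.

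**3. How large a contrast can arise with no adherence effect.** Assumptions, not protocol figures:
- true response is 50% whatever the intake;
- 10% of children have low adherence for unrelated reasons;
- a share sN of non-responders stop for worsening and a share sR of responders stop for cure, and all of these count as low adherence.

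Then low(N) = 0.1 + 0.9·sN and low(R) = 0.1 + 0.9·sR. With response at 50%:
- rate in adherent = [1 − low(R)] / {[1 − low(R)] + [1 − low(N)]}
- rate in low adherence = low(R) / [low(R) + low(N)]

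Example, sN = 0.2 and sR = 0: low(N) = 0.28 and low(R) = 0.10. The adherent rate is 0.90/(0.90 + 0.72) = 55.6%. The low-adherence rate is 0.10/(0.10 + 0.28) = 26.3%.

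| sN | sR | Adherent | Low adherence | Low stratum, of 18 |
|---|---|---|---|---|
| 0 | 0 | 50.0% | 50.0% | 1.8 |
| 0.1 | 0 | 52.6% | 34.5% | 2.6 |
| 0.2 | 0 | 55.6% | 26.3% | 3.4 |
| 0.4 | 0 | 62.5% | 17.9% | 5.0 |
| 0 | 0.1 | 47.4% | 65.5% | 2.6 |
| 0.1 | 0.1 | 50.0% | 50.0% | 3.4 |

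Where only one kind of stopping occurs, the gap is about 18 to 45 points. Its sign depends on which kind it is, and equal shares of both cancel.

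**4. Planned dose per kg.** Dose per kg = min(0.6 × weight, 7.5) / weight.
- 12.5 kg: 0.6 × 12.5 = 7.5 g, or 0.60 g/kg/day (also 0.60 at any lower weight)
- 15 kg: 7.5/15 = 0.50
- 20 kg: 7.5/20 = 0.375
- 25 kg: 7.5/25 = 0.30

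This is a two-fold range, fixed in plan by weight.

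**5. What a weight split could deliver.** If 18 children divided 9 and 9, then 4/9 responders (44%) would have an exact 90% interval of 16.9% to 74.9%. That supports description only.

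**The case against.** The strongest reply is that little is at stake. Section 10.3.4 asks only that rates be obtained; it plans no test, contrast or interaction. The study is exploratory and sized on precision. This stands.

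The dependence on outcome also rests on a denominator that 10.3.4 does not state. If intake is counted only up to the stop date, a child who took every dose until stopping for cure or worsening is fully adherent, and that route largely closes. This stands as a condition on the point. Against it, total scheduled doses is the only denominator the protocol words. Under either definition adherence remains unknown at entry.

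A reader might infer that the analysis will show a false benefit of adherence. For example, with 20 children, 50% response and two stopped for worsening, the rates would be 10/18 = 56% (90% CI 34.1% to 75.6%) against 0/2 (0% to 77.6%). The documents do not support that inference:
- The second interval contains the first, and the one-sided Fisher p-value is C(10,2)/C(20,2) = 45/190 = 0.24.
- The example counts both stopped children as non-responders. The protocol schedules MRI at discontinuation (6.2) and does not impute missing values (10.3.6), but does not say that a child without a 6-month MRI is a non-responder.
- Stopping for cure would push the other way.

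Stopping for poor intake under (vii) is genuine non-adherence and is no evidence that adherence follows response. Nor can the low stratum be said to consist of early stoppers, since no cut-off is set.

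On weight, a reader might infer a broken commitment. Section 2.4 makes evaluation conditional on case numbers, so the gap is a mismatch between the stated purpose and the analysis list. Age is listed and partly tracks weight, but it is not the dose split. A weight split has its own limits: dose per kg is determined by weight and cannot be separated from body size or, largely, from age. Doses may also be adjusted as weight changes (5.3.3), so baseline weight fixes only the planned starting dose per kg.

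**Conclusion.** The point holds in a limited form. Adherence does not belong in a list of entry factors. Counted against total scheduled doses, it can produce a descriptive contrast of roughly 18 to 45 points with no adherence effect, in either direction, in a stratum of about 3 to 5 of 18 children. Those sizes rest on the assumed stopping shares, the 10% background of low adherence and every stopped child falling in the low stratum. What does not rest on them is that the contrast cannot be read as an effect of taking the drug and cannot identify a subpopulation at entry.

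Separately, dose-response is a stated purpose without an analysis in 10.3, although planned dose per kg varies two-fold with a variable already collected.

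The primary analysis is untouched. The consequence is confined to the exploratory information carried into the next study.

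**What to change.** In section 10.3.4:
- Add *baseline body weight: 12.5 kg or less (planned 0.6 g/kg/day) / more than 12.5 kg (planned below 0.6 g/kg/day)*, with response rates and exact 90% intervals as in 10.3.1. Label it descriptive, because dose per kg is confounded with weight and age.
- Remove adherence from the subgroup list. If the information is wanted, report it separately and descriptively, as intake by responder status with the reason for stopping, and state that it is not evidence of an adherence effect.

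The cost is a small text change. Weight is recorded before treatment (6.1), section 5.6 already requires the reason for stopping to be documented, and adherence remains a secondary endpoint under 9.2. The drawback is one more imprecise descriptive split. No dosing or stopping rule changes.
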